**Fig. 1 Fig1:**
[figure not shown]
Participant flow in the Early Home Learning Study and estimated follow-up in the EHLS at School Study

### Power calculation

Given the high rate of retention in the EHLS (78% to 32 week follow-up), we anticipate 65% participation in EHLS at School of eligible participants (i.e., *n* = 212 standard; *n* = 455 *smalltalk* participants). For the comparison of the *smalltalk* to standard programs, the study provides over 95% power to detect a minimum effect size of 0.3, or 88% power to detect an effect size of 0.25, at *p* < 0.05.

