### Recruitment strategy

In EHLS at School, children are eligible to be assessed when they reach 7.5 years of age. Given that toddlers in the original EHLS were aged 12–36 months at baseline assessment over 2010–2013, children are eligible for the EHLS at School Study over a three-year period between 2016 and 2018. Recruitment is currently underway. At study commencement in 2016, all eligible participants (*n* = 990) were sent an information pack describing the study. The pack contained an information letter, contact details form, brochure describing the EHLS at School Study, EHLS at School fridge magnet, flyer describing the findings from the original EHLS Study, and reply paid envelope. Participants were invited to update their contact details via post, email, or phone. Following the mail out, the study team attempted to contact all participants via phone. If participants had already updated their contact details, the purpose of the phone call was to select an age-appropriate children’s book to be posted to the study child. Otherwise, the phone call was used to introduce the study and update participant details (and subsequently arrange for the book to be posted).

Participants are currently being re-contacted prior to the age of eligibility (7.5 years) to arrange and conduct a home visit assessment. Participants who have moved interstate, overseas or who declined a home visit were offered an online or hardcopy option for completing the questionnaire aspects of the assessment. All participants received a $50 gift voucher on completion of the home assessment, or alternatively, a $30 voucher on completion of the parent questionnaire only. To maintain engagement, study children who have not yet been assessed are sent a birthday card each year. Following the home visit or online assessment, and with written parental consent, school teachers are contacted via email and/or phone and invited to complete an online questionnaire.

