### Progress

As of May 2017, the research team has attempted contact with all eligible participants (*n* = 990), of which 637 (64%) have agreed to further contact when their child reaches the eligible age, and 128 (13%) have declined or ‘passively refused’ (i.e., maximum attempts to contact reached with no participation). Further attempts to make contact will continue for the remaining 225 (23%) participants. Assessments have been completed for 373 participants. Of these, 16 participants did not complete the home assessment but instead provided data in the form of the online parent and teacher questionnaires, and consent for data linkage. So far, more than 90% of parents have consented to completion of the online teacher questionnaires, and to data linkage. Based on completed fieldwork, we anticipate a final sample with complete child and parent data of between 60% and 65% of the initial sample.

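### The planned 212 + 455 families are 67.4% of the 990 eligible, not 65%, and an unadjusted test on them has about 85% power at effect size 0.25, not the stated 88%

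*Protocol article*

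**What the plan says.** The Power calculation section of the protocol article states "we anticipate 65% participation in EHLS at School of eligible participants" and translates this directly into 212 standard and 455 smalltalk participants. For that comparison it claims "over 95% power to detect a minimum effect size of 0.3" and "88% power to detect an effect size of 0.25", at p < 0.05. It does not say whether the test is one- or two-sided, and mentions neither covariate adjustment nor a design effect.

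The eligible number is given elsewhere. Recruitment strategy says that "all eligible participants (*n* = 990) were sent an information pack", and Progress repeats 990 as the number of eligible participants whom the team tried to contact. Progress also gives a later forecast: "we anticipate a final sample with complete child and parent data of between 60% and 65% of the initial sample". That base is not defined.

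The power paragraph labels its groups by programme (standard, smalltalk). Statistical analyses defines the primary comparison as any exposure to smalltalk against none.

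**The concern.** The power paragraph treats a percentage and a pair of group sizes as the same quantity, yet with the eligible count printed twice in the article they are not. The two power figures should also follow from one calculation on those group sizes. The simplest calculation returns the figure for 0.3 but not the one for 0.25.

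At stake is the sensitivity that a reader will credit to the study. If the result is null, the stated 88% implies a 12% chance of having missed an effect of 0.25. The unadjusted calculation on the stated sizes gives 15%.

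**Working it through.** **Inputs.** Group sizes 212 and 455, participation 65%, effect sizes 0.25 and 0.3, p < 0.05 (Power calculation). Eligible families 990 (Recruitment strategy; Progress). A two-sided test is my assumption; one-sided is also checked.

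**Participation**

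- Planned total: 212 + 455 = 667.
- Share of eligible: 667 / 990 = 67.4%.
- What 65% would give: 0.65 × 990 = 643.5, about 644. The gap is about 23 families, too many for rounding.
- Base implied by the sizes: 212 / 0.65 = 326 and 455 / 0.65 = 700, together about 1026. Both groups fit 65% of such a base, but the text does not give that number.

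**Power at the stated sizes.** For standardised effect d, the noncentrality is d / √(1/n₁ + 1/n₂). With 212 and 455, √(1/212 + 1/455) = 0.08316.

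- The plan's figure at d = 0.3: 0.3 / 0.08316 = 3.608. Power is 94.98% from the noncentral t and 95.03% from the normal approximation. The stated value is reproduced to rounding.
- The plan's figure at d = 0.25: 0.25 / 0.08316 = 3.006. Power is 85.1% (t) or 85.2% (normal). The stated 88% is not reproduced.

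**What would give about 88% at 0.25**

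| Variant | Power at 0.25 | Comment |
|---|---|---|
| One-sided 0.05, 212/455 | 91.3% | Overshoots |
| Equal split of 667 | 89.8% | Contradicts the stated groups |
| Covariate adjustment, correlation 0.3, 212/455 | about 88% | Not stated in the power paragraph; gives about 96.5% at 0.3 |
| About 727 families at the stated ratio | 88% | 60 more than stated |
| All 38 non-attenders moved to the unexposed group: 250/417 | 87.7% | The 38 are counted in the original trial; 65% of them is about 25, giving 237/430 and 87.0% |

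At 212/455, 88% power corresponds to an effect of about 0.26.

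**Power if 990 is the base** (two-sided t, stated ratio kept, independent families)

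| Sample | Groups | d = 0.25 | d = 0.3 |
|---|---|---|---|
| As stated, 667 | 212/455 | 85.1% | 95.0% |
| 65% of 990, 644 | 205/439 | 83.9% | 94.3% |
| 60% of 990, 594 | 189/405 | 80.9% | 92.5% |

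**Base of the later forecast.** 60% to 65% of 990 is 594 to 644. Of the 1226 in the toddler trial it is 736 to 797. The wording allows either reading, and they differ by more than 140 families.

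**The case against.** The strongest reply is that 88% may be correct for a calculation that the article does not describe. Adjusted analyses are planned and baseline measures exist. With a covariate correlation near 0.3, the stated group sizes give about 88% at 0.25 and more than 95% at 0.3, so a single calculation would match both claims. This stands as a possibility. The supportable statement is therefore that an unadjusted test does not reproduce 88% and that the assumption behind it is not given. A reader might infer that 88% can only come from moving the 38 non-attenders into the unexposed group. The documents do not support that: other routes exist, and the 38 belong to the original trial, not to the projected 667.

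It can also be said that the 65% was applied consistently to an eligible count of about 1026, which Fig. 1 might show. That would explain the group sizes. It would not remove the conflict, because the text twice calls 990 all of the eligible participants.

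Three further inferences go too far:

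- That the claim at 0.3 is also wrong. At the stated sizes it matches to rounding, and falls to 94.3% or 92.5% only if the sample is smaller.
- That the target is already out of reach because only 637 families have agreed. That is an interim count from May 2017, and 225 families were still being contacted.
- That the later forecast must mean 60% to 65% of 990. Its base is undefined, and it concerns complete child and parent data, which is narrower than participation.

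**Conclusion.** The participation rate, eligible count and group sizes in the article cannot all be right together: 667 is 67.4% of 990, and 65% is about 644. The stated power at 0.25 is about 3 points higher than the stated groups give in an unadjusted two-sided 0.05 test (85.1% against 88%). The power at 0.3 is acceptable as written for those groups.

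The size of the problem is modest. Power at 0.25 stays above 80% even at 60% of 990, and the design is not undermined by this point alone. All these values assume independent families, unit-variance outcomes, the stated group ratio and no covariate adjustment. No design effect is included, although the original trial was cluster randomised. Any allowance for clustering would lower them: for 212/455 at 0.25, assumed design effects of 1.1, 1.2 and 1.5 give 82%, 78% and 69%.

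**What to change.** 1. Reconcile the eligible count, the participation rate and the group sizes across Power calculation, Recruitment strategy and Progress. If about 1026 was the base for the sizes, say so and explain how it relates to 990.
2. Restate power for the reconciled sizes: about 85% at 0.25 for 212/455; about 84% at 0.25 and 94% at 0.3 for 65% of 990; about 81% and 92.5% for 60% of 990. Label these as before any design effect. Alternatively, keep 88% and state the assumption that yields it, for example the covariate correlation used.
3. State whether the test is two-sided.
4. Define the base of the 60% to 65% forecast in Progress.
5. Say whether the planned sizes are allocated or exposed groups, since the primary comparison is by exposure.

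The cost is a few sentences and a slightly less favourable power statement, unless the assumption behind 88% is supplied. No additional recruitment and no change to the analysis are needed.

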### Recruitment strategy

In EHLS at School, children are eligible to be assessed when they reach 7.5 years of age. Given that toddlers in the original EHLS were aged 12–36 months at baseline assessment over 2010–2013, children are eligible for the EHLS at School Study over a three-year period between 2016 and 2018. Recruitment is currently underway. At study commencement in 2016, all eligible participants (*n* = 990) were sent an information pack describing the study. The pack contained an information letter, contact details form, brochure describing the EHLS at School Study, EHLS at School fridge magnet, flyer describing the findings from the original EHLS Study, and reply paid envelope. Participants were invited to update their contact details via post, email, or phone. Following the mail out, the study team attempted to contact all participants via phone. If participants had already updated their contact details, the purpose of the phone call was to select an age-appropriate children’s book to be posted to the study child. Otherwise, the phone call was used to introduce the study and update participant details (and subsequently arrange for the book to be posted).

Participants are currently being re-contacted prior to the age of eligibility (7.5 years) to arrange and conduct a home visit assessment. Participants who have moved interstate, overseas or who declined a home visit were offered an online or hardcopy option for completing the questionnaire aspects of the assessment. All participants received a $50 gift voucher on completion of the home assessment, or alternatively, a $30 voucher on completion of the parent questionnaire only. To maintain engagement, study children who have not yet been assessed are sent a birthday card each year. Following the home visit or online assessment, and with written parental consent, school teachers are contacted via email and/or phone and invited to complete an online questionnaire.

### Outcome measures

To address Aims 1 and 3–5, assessed child outcomes include school readiness, child socio-emotional development, language, mental health, self-regulation and physical health, and academic functioning. To address Aim 2, the home environment and parent-child interactions are assessed. Table 1 provides a summary of domains assessed across the EHLS and EHLS at School studies, while Table 2 provides a detailed summary of key measures included in EHLS at School.

**Table 1 Tab1:** Measurement domains assessed in the EHLS and the EHLS at School studies

Domain	Outcome	Data collection method	EHLS			EHLS at School		
			Pre	Po	FU	5y	7.5y	8-10y
*Child and Parent Outcomes*								
Child language and academic	Language, communication	PQ DA DL	✓	✓	✓	✓	✓	✓
	School readiness, English skills	DL				✓		
	Academic skills	TQ DL					✓	✓
Child socio-emotional and general development	Fine motor skills	PQ	✓	✓	✓			
	Personal-social skills	PQ	✓	✓	✓			
	Developmental status	DL				✓		
	Mental health problems, quality of life	PQ CQ TQ DL				✓	✓	
	Social skills	PQ					✓	
	Self-regulation	PQ					✓	
Parenting and home environment	Parent-child interaction	DA	✓	✓	✓		✓	
	Parenting irritability, warmth, consistency, self-efficacy, verbal responsivity	PQ	✓	✓	✓		✓	
	Home learning activities; home literacy environment	PQ	✓	✓	✓		✓	
*Intervention Experiences*								
*smalltalk* exposure	Number of sessions attended, parent engagement, content exposure	Adm		✓				
Other services	Number and type of sessions attended	PQ					✓	
*Covariates*								
Child	Health and disability, temperament	PQ TQ	✓	✓	✓		✓	
Parent	Mental health, quality of life	PQ	✓	✓	✓		✓	
Family	Demographics, family structure, stressful events, social support	PQ	✓	✓	✓		✓	
Services	Use of educational services and child care	PQ	✓	✓	✓		✓	

**TABLE KEY:**
*Pre* Pre assessment, *Po* Post assessment, *FU* Follow-up assessment, *PQ* parent-report questionnaire, *CQ* child-report questionnaire, *DA* direct (child) assessment, *DL* data linkage, *TQ* teacher questionnaire, *Adm* administrative data from group facilitators/home coaches

**Table 2 Tab2:** Summary of key study measures used in the EHLS at School study

Construct	Measurement Details	Data Collection Method and Age
*Child Development*		
School readiness	English Online Interview [44] is administered by teachers at the beginning of the Preparatory/Foundational Year, taking 20–40 min to complete and assessing children’s reading, writing and speaking, and listening skills.	Data linkage to direct teacher assessment of child (5 years)
	School Entrant Health Questionnaire [41] collects data on parents’ concerns and observations about their child’s language, health and wellbeing.	Data linkage to parent-report questionnaire (5 years)
Language	National Institutes of Health Toolbox Picture Vocabulary Test [33] assessing receptive vocabulary.	Direct child assessment (7.5 years)
	Recalling Sentences subtest of the Clinical Evaluation of Language Fundamentals - Fourth Edition [34]; the child is asked to imitate sentences spoken aloud by the researcher.	Direct child assessment (7.5 years)
	Castles and Coltheart Test of Reading Version 2 [35] measuring children’s sounding out ability and whole word recognition.	Direct child assessment (7.5 years)
Academic skills	National Assessment Program – Literacy and Numeracy [45] assesses children’s reading, numeracy, spelling, punctuation and grammar.	Data linkage to national assessment data for Year 3 (age 8) and 5 (age 10)
	Academic Rating Scale [46] assesses children’s academic achievement in terms of language and literacy (10 items) and mathematical ability (8 items).	Teacher questionnaire (7.5 years)
Mental health	Strengths and Difficulties Questionnaire [42] assesses emotional and behavioral problems across 5 subscales (25 items) including hyperactivity/inattention; conduct problems; emotional symptoms, peer problems; and prosocial skills.	Data linkage to parent-report questionnaire (5 years); Parent questionnaire (7.5 years); Teacher questionnaire (7.5 years)
Self-regulation	Approaches to Learning Scale [47] (6 items) assesses children’s eagerness to learn, interest in a variety of things, creativity, persistence, concentration and responsibility, and is rated on a 4 point scale from ‘Never’ to ‘Very often’ or rated as ‘No opportunity to observe this behavior.’	Parent questionnaire (7.5 years); Teacher questionnaire (7.5 years)
	Soothability and Inhibitory Control subscales from the Temperament in Middle Childhood Questionnaire [48] (16 items) assesses children’s rate of recovery from peak distress, excitement, or general arousal, and their capacity to plan and to suppress inappropriate approach responses under instructions or in novel or uncertain situations.	Parent questionnaire (7.5 years)
Quality of life	The Child Health Utility 9D [36] assesses children’s health-related quality of life using 9 questions rated on a 5-point scale. This measure was developed for the use in cost utility analysis (i.e., economic evaluation).	Child assessment (7.5 years)
Physical health	Child global health [49] (1 item) is rated on a 5-point scale from 1 = ‘Excellent’ to 5 = ‘Poor’.	Parent questionnaire (7.5 years)
	Child Health History (3 items) asks parents about hospital stays over past 12 months; current presence of 10 health problems, e.g., ‘wheezing or asthma’; ‘snoring or difficulty sleeping’; and whether ever diagnosed or treated for psychological disorder.	Parent questionnaire (7.5 years)
	Use of health services (1 item) asks parents whether they have used specific health services for their child (e.g., family doctor; Pediatrician; psychological services; dentist), and the cost to the family per visit.	Parent questionnaire (7.5 years)
*Parent-Child Relationship*		
Parent-child interactions	The Sensitive Responding and Mutuality subscales of the Coding of Attachment-Related Parenting scheme [40] assesses attachment-related parenting behaviors rated on a 7-point Likert scale 1 = ‘No evidence’; 7 = ‘Pervasive/extreme evidence’.	Direct child assessment (7.5 years)
Parenting	Parenting warmth [49] (6 items) is rated on a 5-point scale, e.g., “Thinking about the last 6 months, how often do you… hug or hold your child?”	Parent questionnaire (7.5 years)
	Parenting irritability [49] (5 items) is rated on a 5-point scale, e.g., “Thinking about the last 4 weeks, how often have you… lost your temper with your child?”	Parent questionnaire (7.5 years)
	Parenting consistency [49] (5 items) is rated on a 5-point scale, e.g., “When you discipline this child, how often does he/she ignore the punishment?”	Parent questionnaire (7.5 years)
	Parent self-efficacy [49] (4 items) is rated on a 5-point scale, e.g., “How often do you think that this child’s behavior is more than you can handle”.	Parent questionnaire (7.5 years)
	Global parenting self-efficacy [49] (1 item) is rated on a 5-point scale from 1 = “Not very good at being a parent” to 5 = “A very good parent”.	Parent questionnaire (7.5 years)
*Home Environment*		
Home learning activities	Home activities with child (5 items) [47] is rated on a 4-point scale assessing parental engagement of child in home activities that stimulate development, e.g., “Read books to your child”.	Parent questionnaire (7.5 years)
	Home Literacy Environment Scale (6 items) [50] is rated on various scales, e.g., “How many books does your child own?”	Parent questionnaire (7.5 years)
Disorganization	Confusion, Hubbub and Order Scale (6 items) [51] is rated on a yes/no scale, e.g., “The atmosphere in our home is calm”.	Parent questionnaire (7.5 years)
*Parent-Focused Outcomes*		
Psychological distress	Kessler-6 (6 items) [52] rated on a 5-point scale, assesses emotional distress over the past four weeks, e.g., “About how often did you feel nervous?”	Parent questionnaire (7.5 years)
Positive affect	Positive and Negative Affect Schedule, Short Form (5 items) [53].	Parent questionnaire (7.5 years)
Quality of life	The adult version of the Child Health Utility 9D [54].	Parent questionnaire (7.5 years)
*Covariates*		
Demographics	Parent and child age, ethnicity, language spoken, education, income, employment status, family structure and size.	Parent questionnaire (7.5 years)
	Characteristics of the child’s teacher, classroom and school, school culture, physical education, family engagement in school activities; child’s specialized services/needs, absenteeism.	Teacher questionnaire (7.5 years)
Contextual factors	Stressful life events (9 items) [55] over the past 12 months, e.g., “You became pregnant or had a baby; You moved house”.	
	Social support (1 item) is rated on a 4-point scale; 1 = ‘I get enough help’ to 3 = ‘I don’t get any help at all’, and − 1 = ‘I don’t need any help’.	
Student Teacher Relationship	The Pianta Student Teacher Relationship Scale [54] assesses teacher’s perception of teacher-child interactions, including warmth, irritability, compliance, and communication (15 items).	Teacher questionnaire (7.5 years)

Multi-method data collection for the EHLS at School study includes a home visit assessment and an online teacher questionnaire at 7.5 years. The home visit involves completion of a parent questionnaire, parent-child observation, and direct child assessment. Also at the 7.5 year home visit, parent permission is obtained for data linkage to retrospective state educational records of school readiness and academic skills at age 5 years, and prospective national academic test results for assessments conducted when children are in Year 3 (age 8) and Year 5 (age 10) of school. Where possible, measures are consistent across the different methods of assessment. For example, the Strengths and Difficulties Questionnaire, a measure of child socio-emotional development, will be accessed via data linkage to provide parent-report data on child outcomes at age 5, and is also collected at age 7.5 years using parent- and teacher-report questionnaires. Study data are collected and managed using REDCap electronic data capture tools hosted at La Trobe University and the Murdoch Childrens Research Institute (Melbourne, Australia). REDCap (Research Electronic Data Capture) is a secure, web-based application designed to support data capture for research studies [32].

### Direct child assessment measures (home assessment)

The following measures form the direct child assessment and are administered by a researcher during the home visit using an iPad to display or code the child responses.

#### Child language short form

This measure was developed as an iPad application as part of the Centre for Research Excellence in Child Language based at the Murdoch Childrens Research Institute in Melbourne, Australia, to enable population studies to cheaply, reliably and rapidly obtain a measure of language ability. The iPad application has two components: (1) the standardized ‘National Institutes of Health (NIH) Toolbox Picture Vocabulary Test’ [33], which was modified with permission from the United States NIH in order to be delivered on an iPad in an Australian accent, and (2) the standardized Recalling Sentences subtest of the Clinical Evaluation of Language Fundamentals - Fourth Edition [34] (NCS Pearson, Inc. - Reproduced by Permission).

#### Castles and Coltheart test of reading version 2

This is an Australian standardized measure assessing children’s sounding-out ability and whole word recognition in single word reading of regular words (40 items); irregular words (40 items); and non-words (40 items) [35].

